# FASTINA – protocol for a randomised feasibility trial of time-restricted eating to improve response to multiple myeloma therapy

**DOI:** 10.1186/s40814-026-01914-7

**Published:** 2026-09-03

**Keywords:** Multiple myeloma, Time-restricted eating, Fasting, Minimal residual disease

## Abstract

**Supplementary Information:**

The online version contains supplementary material available at https://doi.org/10.1186/s40814-026-01914-7.

## Introduction

Multiple Myeloma (MM) is a clonal plasma cell malignancy with a relapsing–remitting course and therapy resistance. Despite advances, MM remains incurable [23]. Standard treatments include corticosteroids, immunomodulatory drugs (IMiDs), proteasome inhibitors (PIs), monoclonal antibodies (mABs), autologous stem cell transplants (ASCT), and CAR T-cell therapies. Poor long-term prognosis, especially after the first relapse, necessitates supportive strategies to improve outcomes.

Nutritional and metabolic states influence cancer therapy and tumour biology. Dietary components like vitamin C or green tea polyphenols can interfere with anti-MM drugs by reducing PI activity [13, 36]. Beyond nutrients, the metabolic state from caloric restriction may modulate drug absorption and treatment response [25, 33]. FASTINA (Fasting in Staging of MM – Intervention for Nutritional Adherence) specifically evaluates the feasibility of TRE, with nutritional counselling intended to maintain caloric and protein intake during therapy. Fasting and TRE are potential adjuncts due to their metabolic and cellular stress effects [9, 18]. Preclinical studies suggest that nutrient deprivation can decrease insulin and IGF-1 signalling, lower glucose and growth factor levels, increase ketone bodies, and activate autophagy [1, 2] (Fig. 1). This concept of differential stress resistance suggests fasting may protect normal tissues from chemotherapy toxicity while sensitising tumour cells to treatment [15, 26]. Short-term fasting may inhibit pro-growth pathways via ketone-mediated mechanisms, thereby promoting autophagic clearance of damaged cells and impairing tumour cell survival [12]. Fasting may also enhance cytotoxic T-cell activity and reduce immunosuppressive regulatory T-cells [12]. These insights provide a rationale to investigate whether fasting-related interventions can augment tumour kill or reduce toxicity, while recognising that the clinical magnitude and relevance remain uncertain [5, 21]. Pilot studies in solid tumours support the feasibility and safety of short-term fasting during chemotherapy and suggest a potential to reduce toxicity [3, 8, 10, 30], but randomised data remain limited, adherence can decline during repeated cycles, and effects on pathological complete response or severe toxicity have been inconsistent [11, 32].

**Fig. 1 Fig1:**
[figure not shown]
Hypothesised fasting-induced metabolic switch in Multiple Myeloma (MM) cells. Time-restricted eating (TRE) reduces systemic insulin and IGF-1 signalling, potentially decreasing PI3K/AKT activity and mTOR pathway signalling. In parallel, TRE may increase circulating ketone bodies, which can fuel the tricarboxylic acid cycle (TCA) and influence reactive oxygen species (ROS) production. These proposed metabolic changes hold the potential to sensitise MM cells to therapy or impair growth and survival. Adapted from Dal Bello [7] and Luda [19]. Designed with BioRender (Toronto, ON, Canada)

However, TRE is understudied in patients with haematological malignancies such as MM, and the available clinical evidence largely derives from short-term fasting or FMD approaches in solid tumours rather than prolonged daily TRE during intensive MM treatment. Many MM patients receive prolonged therapy and high-dose steroids affecting glucose and IGF-1 levels. Dexamethasone may attenuate fasting-induced reductions in insulin/IGF-1, stimulate appetite, induce hyperglycaemia, and disturb circadian metabolic rhythms. Therefore, steroid timing and dose may confound biological effects attributed to TRE [10, 14, 20]. Nonetheless, as MM remains incurable and deeper responses including MRD negativity are clinically relevant, carefully monitored metabolic-supportive strategies merit prospective evaluation, provided that safety and nutritional adequacy are prioritised. FASTINA addresses this gap by examining if TRE during MM therapy is feasible. We hypothesise that TRE is well-tolerated in MM patients and could deepen the haematologic response.

## Methods

### Trial design

FASTINA is an open-label, parallel-group, single-centre randomised feasibility trial evaluating TRE during standard MM therapy. 54 patients at the University Hospital Schleswig–Holstein (UKSH) – Campus Lübeck, will be randomised 1:1 to two arms: Arm A (experimental): 16:8 TRE (daily 16 h fasting/8 h eating window) for 12 weeks in addition to standard nutritional counselling. Arm B (control): Standard nutritional counselling alone for 12 weeks (no fasting intervention). The 16:8 schedule was selected as a pragmatic compromise between a fasting interval long enough to induce daily metabolic switching and an 8 h eating window that still permits patients to meet energy and protein goals during therapy. More restrictive prolonged fasting was avoided for safety reasons.

All participants continue their standard-of-care anti-MM therapy per guidelines. Trial duration is ≈ 7 months, including 28 d screening, a 12-week intervention during active MM therapy, and 12-week follow-up. Key time points are baseline (T_0_), end of the 12-week intervention (T_1_), and end of the 12-week follow-up (T_2_) (Fig. 2).

**Fig. 2 Fig2:**
[figure not shown]
FASTINA trial schema. Adults with multiple myeloma (MM) scheduled for therapy undergo screening (T_0_; ≤ 28 d) and are randomised 1:1 to experimental arm A (16:8 h time-restricted eating (TRE) + standard-of-care (SoC) nutritional counselling) or control arm B (SoC nutritional counselling alone) during 12 weeks of therapy. Assessments occur at the end of treatment (T_1_) and after a 12-week follow-up (T_2_). Abbreviations: BIA: bioelectrical impedance analysis; BMI: body mass index; EORTC QLQ-C30: European Organisation for Research and Treatment of Cancer Quality of Life Questionnaire-Core 30; FACIT®: Functional Assessment of Chronic Illness Therapy; FACT-G: Functional Assessment of Cancer Therapy-General; MM: multiple myeloma; NRS-2002: Nutritional Risk Screening 2002; SoC: standard of care; T_0_: screening; T_1_: end of treatment; T_2_: end of follow-up

The trial is open-label as blinding of TRE intervention is not possible. Objective endpoints such as minimal residual disease (MRD) assessments will be evaluated blinded to minimise bias. Randomisation is performed to ensure allocation concealment. Stratified randomisation will balance groups for key factors (line of therapy, baseline BMI < 25/≥ 25 kg/m^2^, and gender).

### Participants

The trial includes adults (≥ 18 years) with confirmed MM starting a new line of systemic therapy (first-line or relapsed) per International Myeloma Working Group (IMWG) criteria. Patients must receive standard anti-MM therapy and be medically fit (Eastern Cooperative Oncology Group status 0–2, or 3 if solely due to MM symptoms).

Major exclusion criteria include conditions incompatible with caloric restriction, unintended weight loss, or malnutrition (BMI < 20 kg/m^2^, or cachexia defined as > 5% weight loss in 6 months or > 10% in 12 months) [28], recent major treatments (ASCT within 100 d), history of eating disorders or severe psychiatric illness, and requirement for nutritional support. Active, uncontrolled medical conditions (e.g., insulin-dependent diabetes, severe infections, significant organ dysfunction), known HIV or active hepatitis B/C infection, and pregnancy or lactation are also exclusions. These criteria deliberately select patients without clinically relevant malnutrition or uncontrolled metabolic comorbidity. This is a safety measure for this pilot trial, which limits generalisability to frailer or cachectic MM populations.

All participants provide written informed consent approved by the central ethics committee of the University of Lübeck, compliant with GCP guidelines (2024-182_1). Participants may withdraw at any time and without giving reasons.

### Interventions

Patients randomised to arm A will undergo a 16:8 TRE schedule daily for the 12-week intervention period. The timing of the eating window is flexible but should remain consistent wherever feasible. Outside the designated 8 h window, patients abstain from foods or caloric beverages. Non-caloric fluids are allowed during fasting hours. Adherence is defined as maintaining the 16 h fasting goal on at least 80% of days, with minor deviations permitted. TRE is not intended to induce caloric restriction or weight loss. During the 8 h eating period, patients are counselled to maintain usual energy intake and adequate protein intake, with emphasis on nutrient-dense meals, symptom-adapted meal planning, and widening or pausing the fasting window if intake becomes insufficient. Patients randomised to arm B continue their normal eating pattern.

All patients receive standard nutritional counselling from a nutritionist, including individualised guidance on energy and protein intake during therapy, management of nausea, mucositis, diarrhoea, constipation, dysgeusia or reduced appetite, and healthy eating recommendations. Counselling is identical in both arms, delivered at baseline and reinforced during clinic visits. Additional nutritionist contact is triggered by weight loss, reduced intake, or symptoms compromising dietary adequacy.

All participants maintain a food diary to record eating times and protocol deviations. Arm A patients record the start and end times of their eating window. Arm B patients record their typical mealtimes. The diary also documents symptoms or adverse events (AEs). These logs are reviewed at each visit to assess adherence. To reduce reliance on self-report, adherence and nutritional adequacy will be triangulated with structured interview, body weight, BMI, NRS-2002, BIA-derived body composition angle, and metabolic biomarkers (glucose, ketones, insulin, and IGF-1) measured according to the study schedule. We recognise that biomarkers are supportive rather than definitive adherence measures as they can be influenced by treatment, steroids, and intercurrent illness.

All participants receive standard anti-MM therapy. Various standard treatments are allowed, reflecting real-world practice. Dexamethasone is given per standard dosing in both arms. Steroid dose, schedule, antidiabetic medication, and metabolic symptoms will be documented, and exploratory analyses will consider steroid-containing regimens and timing of biomarker sampling relative to dexamethasone exposure. Supportive treatments (antivirals, bisphosphonates, or transfusions) are permitted as needed. Patients who undergo stem cell harvest or transplant during the study will be handled per protocol. Use of additional dietary supplements is discouraged and must be documented. There are no prohibited medications aside from experimental metabolic therapies.

To ensure patient safety, predefined criteria trigger temporary pause, adaptation, or discontinuation of TRE. Weight loss > 5% from baseline, worsening NRS-2002 score, symptomatic hypoglycaemia, severe dehydration, or clinically relevant electrolyte/metabolic disturbance will prompt investigator and nutritionist review and may lead to temporary widening of the eating window or pausing of TRE. The intervention will be discontinued if arm A patients lose > 10% of baseline body weight or if clinically significant AEs are judged to be related to TRE. Significant AEs will prompt evaluation by the DMC and could lead to modification or termination of the intervention. Patients in arm A who discontinue the fasting protocol continue in the trial for outcome assessment, and their data will inform feasibility results (intention-to-treat (ITT) analysis).

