## Outcomes

### Primary outcomes

Adherence rate: Proportion of patients in the TRE arm adhering to the 16:8 schedule on ≥ 80% of days over the 12-week intervention, reported with a 95% confidence interval (CI).

Therapy response (CR/MRD rate at end of treatment): The combined rate of CR and/or MRD negativity in bone marrow (BM) at end of therapy. CR is defined by IMWG criteria, and MRD negativity at a sensitivity of 10^–5^ by fluorescence-activated cell sorting (FACS) or next-generation sequencing (NGS) on BM aspirate. The fraction will be compared between arms as an exploratory efficacy signal.

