We anticipate minimal missing data for primary endpoints since adherence can be assessed if diary data are > 80% complete. Participants who discontinue TRE or withdraw before adherence can be evaluated will be counted as non-adherent for the feasibility endpoint, and intervention pauses and reasons will be summarised descriptively. If a patient lacks MRD status at T_1_, they will be considered not achieving CR/MRD. Missing data in secondary patient-reported outcomes will be handled by analysing available cases or using imputation methods. For survival, standard censoring at last follow-up is done for those without events. A sensitivity analysis using multiple imputation for missing outcome data will be explored to ensure robustness.

All statistical tests will be two-sided, with *p*-value < 0.05 considered significant for exploratory, hypothesis-generating purposes. No adjustments for multiple comparisons are planned, given the exploratory nature.

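### The Interventions section describes widening in opposite directions for arm A patients (the fasting window in one paragraph, the eating window in another); the wording should be reconciled

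*Protocol article*

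**What the plan says.** All the main statements are in the protocol article.

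- **Schedule (Trial design).** Arm A follows "16:8 TRE (daily 16 h fasting/8 h eating window) for 12 weeks".
- **Counselling (Interventions, first paragraph).** The schedule is not meant to reduce calories or weight. Patients are advised on keeping up energy and protein intake, and the advice ends with "widening or pausing the fasting window if intake becomes insufficient".
- **Safety criteria (Interventions, last paragraph).** "Weight loss > 5% from baseline, worsening NRS-2002 score, symptomatic hypoglycaemia, severe dehydration, or clinically relevant electrolyte/metabolic disturbance will prompt investigator and nutritionist review". That review "may lead to temporary widening of the eating window or pausing of TRE".
- **Adherence rule (Interventions).** "Adherence is defined as maintaining the 16 h fasting goal on at least 80% of days, with minor deviations permitted".
- **First primary outcome (Primary outcomes).** "Proportion of patients in the TRE arm adhering to the 16:8 schedule on ≥ 80% of days over the 12-week intervention".
- **Handling (Statistical methods).** Patients who discontinue TRE, or who withdraw before adherence can be evaluated, "will be counted as non-adherent for the feasibility endpoint, and intervention pauses and reasons will be summarised descriptively". Days on a widened window are not mentioned.

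**The concern.** Two paragraphs of one section tell staff how to adapt the schedule when nutrition is at risk, and on widening they name opposite windows. Read as written, the counselling paragraph lengthens the daily fast of a patient whose intake is already too low. The safety paragraph shortens it.

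Two things are at stake. The first is the instruction itself. The Discussion makes it the central question whether patients can keep to the eating window without loss of calorie and protein intake, and this wording applies to the patients in whom intake is failing. The second is the adherence endpoint. It is tied to the 16 h fast, so the direction of an adaptation can affect whether the adapted days count.

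**Working it through.** **1. Direction of the two instructions.** Let F be fasting hours and E eating hours per day. The Trial design section gives F = 16 and E = 8, so F + E = 24. For any widening of k hours (k > 0):

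| Instruction | F | E | 16 h goal |
|---|---|---|---|
| Widen the fasting window (counselling paragraph) | 16 + k | 8 − k | met |
| Widen the eating window (safety paragraph) | 16 − k | 8 + k | missed, unless k is small enough to be a permitted minor deviation |

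The two widening options move F and E in opposite directions for every k. Pausing appears in both paragraphs and does not conflict.

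**2. Triggers.** The counselling paragraph acts on insufficient intake. The safety paragraph acts on weight loss above 5%, a worse NRS-2002 score, symptomatic hypoglycaemia, severe dehydration, or an electrolyte or metabolic disturbance. The lists are not identical, but a patient with insufficient intake can also lose weight or worsen on NRS-2002, and would then fall under both.

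**3. Days needed for adherence.** 12 weeks × 7 = 84 days. 0.80 × 84 = 67.2, so 68 adherent days are needed and 84 − 68 = 16 may be missed. Suppose that every other day is adherent and that adapted days are judged on the 16 h goal alone:

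- 16 days with a widened eating window: 68/84 = 81.0%, still adherent.
- 17 such days: 67/84 = 79.8%, non-adherent.
- 17 days with a widened fasting window: 84/84 = 100%, adherent.

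**4. Weight of one patient.** The Sample size section plans 27 patients in arm A and a margin of about ±15%. That figure reproduces at an adherence rate of 80%: 1.96 × √(0.8 × 0.2/27) = 0.151. One patient is 1/27 = 3.7 points. The counts below are chosen to lie near the plan's two thresholds, 80% in Sample size and 75% in Progression criteria. They are not forecasts. Intervals are 95% Clopper-Pearson, the method named in Statistical methods.

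| Adherent | Rate | 95% CI | ≥ 80% | ≥ 75% |
|---|---|---|---|---|
| 22/27 | 81.5% | 61.9 to 93.7 | yes | yes |
| 21/27 | 77.8% | 57.7 to 91.4 | no | yes |
| 20/27 | 74.1% | 53.7 to 88.9 | no | no |

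Near the thresholds, the classification of one or two patients decides whether a target is met. The documents give no basis for estimating how many patients would be adapted for 17 days or more.

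**The case against.** The strongest reply is that this is a one-word slip. The phrase closes a sentence about keeping intake up, follows a statement that TRE is not meant to restrict calories, and couples widening with pausing as forms of relief. Lengthening the fast would defeat that sentence. The safety paragraph names the eating window, and experienced staff would probably notice the mismatch. There are also safeguards: reduced intake triggers extra nutritionist contact, weight loss has review and discontinuation thresholds, and a DMC reviews safety data.

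Much of this stands. It makes harm in practice less likely and the correction easy. It does not remove the contradiction, because the article states both instructions and reconciles them nowhere.

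A reader might infer more than the documents support, in three ways:

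- **That the two paragraphs cannot both be followed in the same situation.** The triggers overlap without being identical, and pausing satisfies both. Only widening conflicts.
- **That the plan scores one adaptation in two opposite ways.** It states no scoring rule for adapted days. The primary outcome refers to the 16:8 schedule, and a longer fast with a shorter eating window is not plainly 16:8. Permitted minor deviations could also absorb a small widening of the eating window. The opposite scoring is a consequence of one reasonable reading.
- **That the missing scoring rule is itself a defect.** Such detail may be in the full protocol or the SAP, neither of which is shown. The diaries record the actual start and end of each eating window, so exposure is captured either way.

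**Conclusion.** The point holds as an uncorrected contradiction in an operational, safety-relevant instruction. The two widening options are opposite by arithmetic, and the counselling wording, taken literally, works against its own paragraph. It is probably a slip. It is not a design flaw, and the documents do not show that any patient has been or will be managed by the literal wording.

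The possible effect on the adherence endpoint is limited and conditional. It requires that staff follow the literal counselling text, that adapted days are judged on the 16 h goal, and that an adaptation lasts at least 17 of 84 days when all other days are adherent (fewer if other days are also missed). Each patient so affected moves the rate by 3.7 points. The number of such patients is unknown. How adapted days are scored is a secondary matter that the full protocol or SAP may already settle.

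**What to change.** Reconcile the counselling and safety paragraphs of the Interventions section so that one direction of adaptation is stated in the same terms in both, for example in eating-window hours. Check the full protocol and the patient materials for the same wording and correct it where it occurs. Which instruction applies is for the sponsor's clinicians to decide; this review takes no view.

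While doing so, confirm that the full protocol or SAP says how days on a widened or paused schedule count towards the 80% rule, and add a sentence if it does not.

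The cost is a wording correction, with no new data, visits or patients. Recruitment is ongoing, with 8 of 54 patients randomised at submission, so a correction made at that stage would be in place for the remaining 46.

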### Trial status

Recruitment began in July 2024 and is ongoing. At the time of submission to *Pilot and Feasibility Studies*, 8 patients have been randomised. Based on an expected recruitment rate of approximately 10 participants per year, recruitment is anticipated to be completed by December 2029. Recruitment rate, screen-failure reasons, refusal, dropout, and non-adherence will be reported as feasibility outcomes. If the predefined safety and adherence criteria are met, a multicentre phase II trial will be pursued to improve recruitment, external validity and statistical power.

### Progression criteria

Progression to a definitive randomised efficacy trial will be considered if the pilot study demonstrates: (I) recruitment of at least 80% of the planned sample within the recruitment period, (II) retention of ≥ 85% of participants until the primary endpoint, (III) adherence to the time-restricted eating intervention in ≥ 75% of intervention participants, (IV) ≥ 90% completeness of key clinical and patient-reported outcome data, (V) no unexpected intervention-related safety concerns, and (VI) overall acceptability of study procedures for participants and investigators. These criteria will be interpreted collectively to determine whether modifications are required before initiating a full-scale efficacy trial.

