## Sample size

The sample size for this trial was based on precision for the adherence endpoint, not statistical power for efficacy. We set a target that ≥ 80% of patients in the TRE arm must achieve adequate adherence for the intervention to be deemed feasible. Using a one-sample proportion calculation, enrolling 27 patients in the experimental arm allows the adherence rate to be estimated with a margin of error of approximately ± 15% at 95% CI. Therefore, 54 patients were chosen to assess feasibility with adequate precision. This sample also matches typical pilot trial sizes in oncology and is sufficient to identify major safety or compliance issues.

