## Statistical methods

All analyses will follow the ITT principle. A per-protocol (PP) analysis will be performed as a sensitivity analysis. Safety analyses will include all patients who started the intervention or control and may be stratified by actual fasting behaviour if crossovers occur.

For the primary endpoint feasibility, the adherence rate in arm A will be calculated as patients with ≥ 80% fasting-day compliance divided by total patients in arm A, with a 95% CI (Clopper-Pearson). No hypothesis test is needed for this single-arm feasibility measure, and we will compare the observed adherence to our target threshold.

For the preliminary efficacy endpoint of CR with MRD negativity at T_1_, proportions between both arms will be compared using a chi-square or Fisher’s exact test to explore differences. We will estimate the absolute difference in CR/MRD rates between arm A and B with CI. To adjust for potential imbalances and our stratification factors, we will perform logistic regression: The dependent variable will be CR/MRD-negative status, and independent variables will include treatment arm, line of therapy, baseline BMI category, and gender. The logistic regression will provide an adjusted OR with a 95% CI for achieving CR/MRD negativity, yielding a hypothesis-generating effect size. We will examine MRD negativity alone and CR (regardless of MRD) separately as post hoc analyses.

Secondary endpoint analysis will be descriptive and exploratory: Response categories (VGPR, PR, SD) will be tabulated by arm. Survival endpoints (PFS, OS) will be plotted using Kaplan–Meier curves. Continuous measures like weight, BMI, and lab values will be analysed using mixed-effects models or paired t-tests within arms and compared between arms by analysis of covariance (ANCOVA), adjusting for baseline. AEs will be summarised by category and grade. QoL and fatigue scores will be analysed by calculating changes from baseline to T_1_. Mean changes will be compared between arms using t-tests or non-parametric tests if data are not normally distributed. Exploratory biological endpoints will be analysed for hypothesis-generation.

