This study has limitations common to pilot trials [32]. The single-centre design, anticipated slow recruitment, small sample size, and treatment heterogeneity could dilute observable effects and will preclude definitive efficacy conclusions. We enrol both newly diagnosed and relapsed patients, which introduces variability in prognoses and treatments. Additionally, the open-label design could introduce bias from placebo effects or behavioural differences in self-reported outcomes. We equalised contact by providing counselling to both arms, but some bias is inevitably possible. Food diaries are vulnerable to reporting bias, therefore, diary data will be interpreted together with body composition and metabolic biomarkers, while acknowledging that these objective measures are not specific for TRE adherence. Another limitation is the short intervention duration of 3 months – chosen to coincide with typical induction therapy length and to mitigate dropout – which may not be sufficient to influence long-term outcomes like PFS [32]. It will, however, capture initial response. We also acknowledge that our patient population is selected by design – excluding those with frailty, significant weight loss, cachexia or malnutrition – so results may not generalise to all MM patients, especially those who are older or have poor nutritional status [4].

If FASTINA demonstrates feasibility, acceptable safety, and a preliminary response signal, a larger, multicentre phase II trial focusing on efficacy with response rate or PFS as primary endpoint should follow. It could incorporate refinements from FASTINA, such as optimal fasting timing, objective adherence tools, patient education strategies to improve adherence, and robust patient-reported outcome measures. In parallel, the biological samples from FASTINA may yield insights that open new research questions – for instance, if fasting is found to substantially reduce IGF-1 during therapy, one could investigate combining TRE with drugs targeting the IGF-1 pathway [27]. Or if TRE appears to improve T-cell counts or function, it might synergise with immunotherapies like checkpoint inhibitors or CAR-T cells – a hypothesis for future trials [16, 17, 24, 34, 35].

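### The required share of adherent TRE patients is 75% in the progression criteria and 80% in the sample-size section, and the analysis section does not say which applies

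*Protocol article*

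**What the plan says.** Three sections of the Protocol article bear on the adherence decision.

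- **Progression criteria**, third of six: "III) adherence to the time-restricted eating intervention in ≥ 75% of intervention participants".
- **Sample size**: "We set a target that ≥ 80% of patients in the TRE arm must achieve adequate adherence for the intervention to be deemed feasible". The same section states that "enrolling 27 patients in the experimental arm" gives a "margin of error of approximately ± 15% at 95% CI".
- **Statistical methods**: the adherence rate is adherent patients over all patients in arm A, with a Clopper-Pearson interval and no hypothesis test, and "we will compare the observed adherence to our target threshold". No figure is given there.

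A further 80% appears under Primary outcomes: "Proportion of patients in the TRE arm adhering to the 16:8 schedule on ≥ 80% of days over the 12-week intervention". It defines when a single patient counts as adherent. The 75% and the 80% at issue here are both shares of patients, so the discrepancy does not come from confusing these two levels.

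The consequences are described in more than one way. Trial status says: "If the predefined safety and adherence criteria are met, a multicentre phase II trial will be pursued". The Discussion says: "If FASTINA demonstrates feasibility, acceptable safety, and a preliminary response signal, a larger, multicentre phase II trial" should follow. The six progression criteria contain nothing on response.

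**The concern.** Adherence is a primary outcome and the only basis for the sample size. Because no test is planned, the conclusion on feasibility rests on setting an observed proportion against a threshold. If the threshold has two values, a result between them meets one section and fails another.

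The trial is open-label and had randomised 8 patients when the article was submitted. If the figure is settled only at analysis, it can be settled by people who already know roughly where the result lies. Even if the choice were made in good faith, a reader of the final report could not tell.

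**Working it through.** **Inputs.** Arm A size 27, margin of about ±15 points, 95% confidence and the 80% threshold (Sample size); 75% threshold (Progression criteria); denominator all arm A patients (Statistical methods).

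**1. Reproduce the stated sample size.** For a normal-approximation interval, n = z² p(1 − p) / d², with z = 1.96 and d = 0.15. The half-width at n = 27 is z √(p(1 − p)/27).

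| Expected rate p | n for ±15 points | Half-width at n = 27 |
|---|---|---|
| 0.80 | 3.84 × 0.16 / 0.0225 = 27.3 | 15.1 points |
| 0.75 | 3.84 × 0.1875 / 0.0225 = 32.0 | 16.3 points |

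The stated 27 and ±15 points reproduce at an expected rate of 80%. The section does not name the expected rate, so this is an inference, but it ties the sample size to the 80% target rather than to the 75% in the progression criteria.

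**2. Turn the thresholds into counts.**

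- 20/27 = 74.1%: fails both.
- 21/27 = 77.8%: meets 75%, fails 80%.
- 22/27 = 81.5%: meets both.

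The two rules therefore disagree at exactly one count, 21/27. Its Clopper-Pearson interval is 57.7% to 91.4%.

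**3. How often the choice matters.** Let X be the number adherent, binomial with n = 27 and true rate p. For example, at p = 0.80, P(X = 21) = C(27,21) × 0.80²¹ × 0.20⁶ = 0.175.

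| True rate p | P(X ≥ 21), 75% rule | P(X ≥ 22), 80% rule | P(X = 21) |
|---|---|---|---|
| 0.70 | 25.6% | 13.6% | 12.1% |
| 0.75 | 47.1% | 29.9% | 17.2% |
| 0.80 | 71.3% | 53.9% | 17.5% |
| 0.85 | 90.1% | 79.0% | 11.1% |

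These are probabilities of meeting the adherence threshold alone. They are not probabilities of progression, which depends on six criteria.

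**4. If arm A does not end at 27.** The first progression criterion accepts 80% of the planned sample: 0.80 × 54 = 43.2, or about 22 in arm A. There 17/22 = 77.3% is the discordant count. For every arm size from 21 to 28, one or two counts lie between 75% and 80% (at 24, for example, 18 and 19). The gap does not disappear with a different enrolment.

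**The case against.** The strongest defence is that the two figures do different jobs. Only one section is headed Progression criteria; the 80% in Sample size is the bar for calling the intervention feasible and sits within a precision argument. A feasibility target with a lower floor for progression is a possible design. But the article does not describe such a two-tier scheme, and Statistical methods refers to a single threshold. The defence offers a way to reconcile the text; it does not show that the text is already consistent.

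It is also fair to say that the difference is one count at full enrolment, that the interval around 21/27 covers both thresholds, and that the rate will be reported with its interval in any case. This limits the size of the problem.

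Two stronger readings are tempting, and the document does not support them.

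- *A reader might infer that one result would mean both proceed and stop.* The progression criteria say only that a definitive trial will be considered, and that the six items are weighed together to see whether changes are needed. At 21/27 no section forces a stop. The Sample size section defines feasibility, not progression.
- *A reader might infer that the Discussion makes a response signal a condition for the next trial.* The Discussion and its concluding paragraph say what would follow from, or be justified by, a favourable set of results. They do not say that the next trial requires a signal. Primary outcomes and Statistical methods treat the CR/MRD comparison as exploratory or hypothesis-generating, and the Discussion itself says it is there to estimate effect sizes and variability for a later trial. Power calculations for a response gate would test a rule that the plan does not contain.

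**Conclusion.** Wrong as written, with a narrow practical effect. The same arm A proportion has two thresholds, 75% and 80%, and the analysis section does not say which it uses. With 27 patients they differ only at 21/27, which meets the third progression criterion but falls short of feasible as defined under Sample size. That count has a probability of about 17% if true adherence is 75% or 80%, and 11% to 12% at 85% or 70%. At true adherence of 80%, the threshold is met with probability 71% or 54%, depending on the figure used.

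These figures assume 27 patients in arm A, all in the denominator, independent outcomes with a common adherence probability, and comparison of the point estimate with the threshold.

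The differing descriptions of the next step in Trial status, Progression criteria and the Discussion are a minor matter of alignment.

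**What to change.** 1. Choose one adherence threshold and state it identically in Progression criteria, Sample size and Statistical methods, as a percentage of all arm A patients. The count at full enrolment (21/27 for 75%, 22/27 for 80%) can be added as an illustration; the percentage should govern, because arm A may not end at 27. If two tiers are intended, say so and give each its consequence.
2. State in Statistical methods that the point estimate, not a confidence limit, is compared with this threshold.
3. If 75% is kept, restate the precision under Sample size as about ±16 points at an expected rate of 75% with 27 patients. If 80% is kept, the present precision statement stands.
4. Minor: make Trial status refer to the Progression criteria, and word the Discussion and its conclusion so that the CR/MRD estimate informs the design of the next trial and is not read as a condition for it.

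The cost is a wording amendment, with no added patients, visits or data. It should be made before the adherence results are known.
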